## **4. STUDY POPULATION**

### **4.1. Participants**

Up to 75 men and women will be recruited to participate in a 2-week pilot study involving infant formula preparation. Participation is open to all adult individuals.

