## **9. DATA ANALYSIS PLAN**

### **9.1. Power Analysis**

We will test the primary aim to assess if the RFPM can accurately estimate simulated food intake compared to the gold standard— directly weighed foods. Power calculations were performed on the main outcome variable, which is the simulated food intake. Two measures of food provision will be obtained: powdered formula and prepared formula, the latter of which is created by adding water to the powdered formula. Food waste is defined as the liquid formula remaining in a bottle after simulating feeding (random discard of 10-90% of prepared bottle). Food intake is food provision minus food waste. A secondary aim is to evaluate the inter- and intra- individual variability in infant formula preparation so this study is also appropriately powered to detect differences in the grams of powdered dry formula in the bottle.

A power analysis was conducted for the Bland and Altman procedure that will be used to determine if the RFPM significantly over or underestimates food provision, waste, or intake and if the error associated with the RFPM varies over the amount of food provision, waste, and intake. Determining if error variance differs over levels of intake is critical to examining validity and accuracy; hence, the sample size was established based on the regression analysis used to do so since it required the largest number of participants.

A power analysis was conducted for the Bland-Altman regression analysis. The power analysis indicated that an  $R^2$  of .14 can be detected with 53 participants (power = .80) and this is considered acceptable based on studies that used Bland-Altman analysis on biological parameters. This research indicates that poor measures frequently have  $R^2 \geq 0.16$ ; therefore, sample size of 53 would yield satisfactory statistical power in the analyses for the primary aim. The primary aim was used for power calculations since sample size was based on the least powered endpoint (i.e. aim 1).

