Paired dependent t-tests will determine if the RFPM has significant error; i.e., if RFPM estimates differ significantly from weighed food. Variance estimates for the power analyses were obtained from our laboratory [10] and assumptions included alpha equal to 0.05, two-tailed tests, and anticipated sample size with 5% attrition (56 subjects will begin the study anticipating we will have a final sample size of 53 subjects.) Again, power of .80 was considered acceptable.

Power for intake (provision minus waste) of prepared formula was calculated with variance estimates for intake of beverages from our laboratory. As illustrated in Table 2, with 53 participants and the assumptions listed above, we have 80% power to detect a 4.95 g difference between RFPM estimated and directly weighed prepared formula intake.

| Table 2. Effect Size Calculations for Intake (Provision minus Waste) of Beverages |                                                     |        |       |             |
|------------------------------------------------------------------------------------------|-----------------------------------------------------|--------|-------|-------------|
| n per group                                                                              | Minimum detectable difference in formula weight (g) | SD (g) | Power | Effect Size |
| 30                                                                                       | 6.80                                                | 9.71   | 0.80  | 0.70        |
| 40                                                                                       | 5.83                                                | 9.71   | 0.80  | 0.60        |
| 45                                                                                       | 5.44                                                | 9.71   | 0.80  | 0.56        |
| 50                                                                                       | 5.15                                                | 9.71   | 0.80  | 0.53        |
| 53                                                                                       | 4.95                                                | 9.71   | 0.80  | 0.51        |
| 55                                                                                       | 4.86                                                | 9.71   | 0.80  | 0.50        |

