| 60                                                                                       | 4.66                                                | 9.71   | 0.80  | 0.48        |

With 53 subjects, we can detect a difference of 2.57 g (effect size or ES = 0.55, Table 3) between the RFPM's estimate and the weighed value for provision of powdered infant formula. This power analysis relied on variance estimates for condiments from our laboratory [10] which are similar to infant formula. This effect size of 2.57 grams reflects a very small amount of formula, indicating that the study is sufficiently powered. We recognize that predicting that no significant differences will be detected is problematic, though the proposed sample size and data analytic plan represents a viable alternative to equivalence tests that require very large sample sizes.

| Table 3. Effect Size Calculations for Food Provision (Dry Weight) |                                                     |        |       |             |
|--------------------------------------------------------------------------|-----------------------------------------------------|--------|-------|-------------|
| n per group                                                              | Minimum detectable difference in formula weight (g) | SD (g) | Power | Effect Size |
| 30                                                                       | 3.51                                                | 4.68   | 0.80  | 0.75        |
| 40                                                                       | 3.00                                                | 4.68   | 0.80  | 0.64        |
| 45                                                                       | 2.81                                                | 4.68   | 0.80  | 0.60        |
| 50                                                                       | 2.62                                                | 4.68   | 0.80  | 0.56        |
| 53                                                                       | 2.57                                                | 4.68   | 0.80  | 0.55        |
| 55                                                                       | 2.53                                                | 4.68   | 0.80  | 0.54        |
| 60                                                                       | 2.39                                                | 4.68   | 0.80  | 0.51        |

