## 9.2. Data Analysis

Paired dependent t-tests will determine if the RFPM has significant error; i.e., if RFPM estimates differ significantly from weighed food, and the Bland and Altman regression procedure will be conducted to determine if error variance differs over the amount of food provision, waste, and intake. Provision, waste, and intake will be compared using paired t-tests. Also, provision, waste, and intake will be compared using the Bland-Altman method. Statistical significance will be set at an alpha of 0.05.

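### Accuracy of the RFPM is to be judged by non-significant differences, and the sample-size reason for declining an equivalence test is unsupported and fails at the plan's own figures

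*Protocol*

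**What the plan says.** Protocol section 2.4 sets the primary aim: whether the RFPM estimates simulated intake accurately against direct weighing. Section 9.2 fixes how this is decided: "Paired dependent t-tests will determine if the RFPM has significant error; i.e., if RFPM estimates differ significantly from weighed food". A Bland-Altman regression accompanies the t-tests to see whether error changes with the amount. Section 9.2 also lists a Bland-Altman comparison of provision, waste and intake. One alpha of 0.05 applies throughout, and no acceptable bias, slope or limit of agreement is stated.

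Section 9.1 says that "sample size of 53 would yield satisfactory statistical power in the analyses for the primary aim". For the t-tests, "assumptions included alpha equal to 0.05, two-tailed tests", and for intake "we have 80% power to detect a 4.95 g difference between RFPM estimated and directly weighed prepared formula intake" (SD 9.71 g, Table 2). For powder the detectable difference is 2.57 g (SD 4.68 g, Table 3), which the text describes as very small. The section then admits that forecasting a lack of significant differences is a problem, and keeps the approach because "the proposed sample size and data analytic plan represents a viable alternative to equivalence tests that require very large sample sizes". Recruitment is capped in section 4.1: "Up to 75 men and women will be recruited to participate in a 2-week pilot study".

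**The concern.** A test built to detect a difference cannot by itself show that the difference is small. If a non-significant result is read as accuracy, the incentive runs backwards: noise and small numbers help the method pass, while a precise study may reject it for a trivial bias. The regression has the same weakness, because a slope that just misses significance is compatible with a strong relation between error and amount.

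The protocol sees this problem and sets the usual remedy aside for one stated reason, the sample size that equivalence testing would need. That reason can be checked against the protocol's own N and SDs. If it fails, the primary aim is left without an affirmative test for no good cause.

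**Working it through.** **Inputs (protocol sections 9.1 and 4.1).** N = 53 completers; two-sided alpha 0.05; power 0.80; intake 4.95 g with SD 9.71 g; powder 2.57 g with SD 4.68 g; 5% attrition; cap 75. The protocol does not say whether the SDs are of the paired difference or of one method. One paired difference per participant is assumed, as in the power tables.

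**The plan's own figures.**
- Paired t-test, noncentrality = difference × √n / SD. Intake: 4.95 × √53 / 9.71 = 3.71, power 95.4%. Powder: 2.57 × √53 / 4.68 = 4.00, power 97.5%.
- Two-sample t-test with 53 per group, noncentrality = difference / (SD × √(2/n)). Intake: 2.62, power 73.9%. Powder: 2.83, power 80.0%.
- So Table 3 reproduces only as a two-sample calculation, and Table 2 reproduces as neither. Both tables are headed per group although the design is paired, so the meaning of the SDs matters below.
- Attrition: 53 / 0.95 = 55.8, hence 56, which reproduces.

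**What non-significance shows.** With SD 9.71 g as the SD of the difference, a true intake bias of 3 g is non-significant with probability 74% at n = 20, 40% at n = 53 and 25% at n = 75. The smaller the study, the more often the method passes.

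For the regression at n = 53, the critical correlation is r = 0.271 (R² = 0.073). On Fisher's scale the upper 95% limit is atanh(0.271) + 1.96/√50 = 0.278 + 0.277 = 0.555. This is r = 0.504, or R² = 0.25, above the 0.16 that section 9.1 associates with poor measures.

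**Equivalence at the plan's own numbers.** Two one-sided paired tests (TOST), alpha 0.05 each, true bias 0, margins set to 4.95 g and 2.57 g (assumption).
- Standard errors: 9.71/√53 = 1.334 g and 4.68/√53 = 0.643 g. With t(0.95, 52 df) = 1.675, the 90% CI half-widths are 2.23 g and 1.08 g, well inside the margins.
- Approximate power = 2Φ(margin/SE − 1.675) − 1. Intake: 2Φ(3.711 − 1.675) − 1 = 0.958. Powder: 2Φ(3.998 − 1.675) − 1 = 0.980. Integrating over the sample SD gives 95.6% and 97.9%.
- Approximate n for 80% power = (1.645 + 1.282)² × (SD/margin)². Intake: 8.56 × 3.85 = 33. Powder: 8.56 × 3.32 = 28. The exact t-based values are 35 and 30.

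**Sensitivity.**

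| Case (one-sided alpha 0.05) | Intake: power at 53; n for 80% | Powder: power at 53; n for 80% |
|---|---|---|
| SD of the difference, bias 0 | 95.6%; 35 | 97.9%; 30 |
| Per-method SD, correlation 0.25, bias 0 | 82.2%; 51 | 88.5%; 44 |
| Per-method SD, correlation 0 (SD × √2), bias 0 | 65.5%; 68 | 74.8%; 59 |
| SD of the difference, bias half the margin | 57%; 97 | 63%; 84 |

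In the third row, 68 / 0.95 = 71.6, so 72 recruits for intake, and 59 / 0.95 = 62.1, so 63 for powder. Both are within 75.

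Tighter margins at zero bias, SD of the difference: intake needs 92 at 3 g, 204 at 2 g and 809 at 1 g. For powder, 10% of the 8.8 g scoop (0.88 g, an illustration) needs 244.

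**The case against.** A reader might infer that the protocol's own N and SDs disprove the statement about large samples. They do not. The protocol states no equivalence margin. The calculation borrows the detectable differences, and only the 2.57 g figure is called very small in the text. Even that is 29% of the powder for a 2-ounce bottle (2.57/8.8). A margin of 2 g for intake or 0.88 g for powder needs over 200 participants, and a true bias of half the borrowed margin would exceed the cap of 75. The sponsor's statement can therefore be true for a strict margin. What stands is that it is given without a margin or a calculation, and that it fails at the only differences the protocol offers.

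A reader might also infer that equivalence testing would catch biases that the t-test misses. At these numbers it would not. With a 4.95 g margin and N = 53, TOST accepts a true 3 g bias 42% of the time and a 2 g bias 70%, against 40% and 69% non-significance for the t-test. The gain is a claim tied to a stated tolerance, with evidence that strengthens as precision improves. It is not a lower pass rate at these particular biases.

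Nor are significance tests the whole plan. A Bland-Altman comparison is also listed, and how limits of agreement are reported may properly sit in an analysis plan that is not shown. The criticism is confined to what the protocol does fix: significance as the criterion for error, no acceptance limit, and an express decision against equivalence. That this is an openly caveated pilot with N set by the regression is fair context. It does not make non-significance evidence of accuracy.

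**Conclusion.** The point holds in this limited form. The protocol reads accuracy from non-significant paired t-tests and a non-significant regression slope, attaches no acceptance limit to the Bland-Altman comparison, and rejects equivalence testing for a reason it does not support. At margins equal to its own detectable differences, with zero true bias and one-sided alpha 0.05, the planned 53 participants give about 96% power (intake) and 98% (powder) if the SDs are of the paired difference. If they are per-method and uncorrelated, power at 53 is 66% and 75%, and the required number still fits under the cap.

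The conclusion rests on the borrowed margins, on small true bias and on one difference per participant. It does not show that 53 participants suffice for any margin that might be chosen.

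**What to change.** Before analysis:

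1. State and justify a margin for mean bias in intake and another for powder provision, in grams or as a percentage of the weighed amount.
2. Declare the RFPM accurate for each only if the 90% CI of the mean RFPM-minus-weighed difference lies wholly inside its margin.
3. Set a bound for the Bland-Altman slope and judge proportional bias by whether the slope's CI lies within it.
4. Keep the t-tests as descriptive.
5. State whether 9.71 g and 4.68 g are SDs of the paired difference or of one method.
6. Delete the sentence on equivalence sample sizes, or replace it with the power at the chosen margin.

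The cost is protocol wording and margins that must be defended in advance; the data collected are the same. At margins of 4.95 g and 2.57 g with zero bias, no participants are added if the SDs are of the difference. Under the uncorrelated per-method reading, up to 72 recruits would be needed, within the cap. A tight or percentage margin may leave power below 80% at N = 53, and the protocol should then say so.

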## 9.2. Data Analysis

Paired dependent t-tests will determine if the RFPM has significant error; i.e., if RFPM estimates differ significantly from weighed food, and the Bland and Altman regression procedure will be conducted to determine if error variance differs over the amount of food provision, waste, and intake. Provision, waste, and intake will be compared using paired t-tests. Also, provision, waste, and intake will be compared using the Bland-Altman method. Statistical significance will be set at an alpha of 0.05.

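### The Bland-Altman regression is given the job of testing error variance, but as sized it is in all likelihood a test of a trend in mean error, so its power and a null result say nothing about constant variance

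*Protocol*

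**What the plan says.** Section 9.2 of the protocol lists paired t-tests for mean error and then says that "the Bland and Altman regression procedure will be conducted to determine if error variance differs over the amount of food provision, waste, and intake". It also says that the three quantities will be compared by the Bland-Altman method. It names no separate test or model of error variance.

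Section 9.1 describes the purpose of the same procedure in two ways. One is whether the method over- or underestimates and "if the error associated with the RFPM varies over the amount of food provision, waste, and intake". The next sentence turns to variance: "Determining if error variance differs over levels of intake is critical to examining validity and accuracy". It continues that "the sample size was established based on the regression analysis used to do so since it required the largest number of participants". The power statement for that regression is that an R² "of .14 can be detected with 53 participants (power = .80"), and poor measures are said to have R² of 0.16 or more. The regression equation is not written out in either section.

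**The concern.** Regressing the difference between two methods on amount estimates how the average difference moves with amount. Its slope and R² describe proportional bias. Whether errors scatter more widely at large amounts than at small ones is a different question, and the slope can be zero whatever the answer.

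The protocol ties the second question to what appears to be the first test, calls the question critical, and rests the sample size on it. A reader following section 9.2 would take a non-significant slope as evidence that error variance is constant, although nothing had tested that. The design leaves room for a changing spread: bottles run from 2 to 8 fluid ounces and the discard from 10 to 90%, so intake covers a wide range. The protocol itself makes no claim about whether the spread will change.

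**Working it through.** **Inputs from the protocol.** R² = .14, N = 53, power .80 (section 9.1). Alpha 0.05, two-sided: section 9.1 states that "assumptions included alpha equal to 0.05, two-tailed tests, and anticipated sample size with 5% attrition" in its paragraph on the t-tests, and I take it to cover the regression; section 9.2 also sets alpha at 0.05. SD 9.71 g for prepared-formula intake (Table 2). Bottles of 2, 4, 6 and 8 fl oz, with 8 bottles at Visit 1 and 4 at Visit 2 (sections 6.2 and 6.3), so 8 + 4 = 12 per participant.

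**Step 1: reproduce N = 53 as a test of one slope.**
- Fisher z: N = ((1.960 + 0.842) / atanh(√0.14))² + 3 = (2.802 / 0.3933)² + 3 = 53.75, so 54. Power at N = 53 is 0.794.
- Noncentral F, one fixed predictor: f² = 0.14 / 0.86 = 0.163, which gives N = 51. Power at N = 53 is 0.822.
- Bivariate-normal simulation (100,000 runs): power 0.803 at N = 53.
- With 2 or 3 predictors the noncentral F gives N = 63 or 72, so 53 fits a one-predictor regression only.
- Attrition: 53 / 0.95 = 55.8, so 56 starters, as stated.

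The plan's figure is therefore correct for a single linear slope.

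**Step 2: what that regression responds to.** Assumptions: N = 53, one value per participant, about 30 g per fl oz, so intake runs from 2 × 30 × 0.1 = 6 g to 8 × 30 × 0.9 = 216 g and is taken as uniform over that range; overall error SD 9.71 g; 20,000 runs. Entries are the percentage of runs significant at 0.05.

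| Error pattern | Error on weighed amount | Error on mean of both methods | Absolute residuals on mean |
|---|---|---|---|
| Constant SD, no trend | 5.0 | 8.7 | 5.2 |
| SD rises 2-fold, no trend | 5.3 | 9.3 | 38 |
| SD rises 3-fold, no trend | 5.9 | 9.5 | 70 |
| SD rises 4-fold, no trend | 6.3 | 10.1 | 84 |
| SD rises 8-fold, no trend | 7.0 | 10.5 | 96 |
| Mean trend with R² = .14, constant SD | 81 | 93 | 5 |

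The slope test finds a mean trend and stays close to its null rate when only the spread changes. The absolute-residual test does the reverse.

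**Step 3: sensitivity to the error model and the unit of analysis.** Here bottle size is drawn from the four sizes, the discard is uniform on 10 to 90%, there is no mean trend, and error SD is 10% of intake.
- One bottle per participant: absolute residuals are significant in about 99% of runs and difference on mean in about 23%. With constant error, difference on mean already rejects in about 9 to 11%, because the error is also part of the predictor. This error model implies an SD that changes 216 / 6 = 36-fold over the range, which is extreme.
- Twelve bottles averaged per participant: absolute residuals about 20%, difference on mean about 15%. Every participant prepares the same set of sizes, so averaging removes most of the range in amount.

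**The case against.** The equation is inferred. A one-predictor R² with N = 53 would fit a regression of absolute differences on amount as well as one of signed differences, so the arithmetic alone does not settle which was meant. That stands, and it is why the conclusion is put as very likely and not as certain. What tips it is section 9.1's description of the procedure as asking whether the error itself varies with amount.

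Error variance may also be loose wording for proportional bias. On that reading method, power and intent agree, and the fault is a phrase used in both sections. This is plausible. It changes the repair from adding a test to correcting a description, but the text still needs correcting, because it is the stated basis for the sample size.

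A reader might infer more: that the variance question will go wholly unexamined, or that the study will report one pair of limits of agreement in grams that is wrong at both ends of the range. The protocol supports neither. The Bland-Altman method is listed separately, and a plot of differences against amount could show fanning by eye. Limits of agreement are never mentioned. A statistical analysis plan, not shown, could add a formal test. Nor is 99% against 23% a general measure of the loss, since it needs one bottle per participant and strictly proportional error.

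What remains is not an omission left to a later plan. The protocol itself assigns a named question to a named method that, as sized, very probably does not answer it.

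**Conclusion.** The stated purpose and the apparent method do not match, and sections 9.1 and 9.2 must be reconciled. N = 53 is correct for detecting a linear trend in mean error with R² = .14. It gives no power statement for a change in error variance, and a non-significant slope must not be read as constant variance.

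The size of the gain from a proper variance test depends on the error pattern and on the unit of analysis, neither of which the protocol states. Under the assumptions above, detection runs from about 20% (12 bottles averaged) through 38 to 96% (SD rising 2- to 8-fold, one value per participant) to about 99% (SD proportional to intake, one bottle each). The slope test is significant in 5 to 23% of the same no-trend scenarios, and those significant results would be misread as a trend.

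This should be fixed, but it does not undermine the design, the sample size or the paired t-tests.

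**What to change.** In sections 9.1 and 9.2, describe the existing regression, its R² and its N = 53 as the test of proportional bias, and write out the equation. Then either drop the claim about error variance or add a test that addresses it: a regression of the absolute residuals on amount, run at bottle level with allowance for repeated bottles from the same participant. Bottle level matters, because averaging over the 12 bottles removes most of the power. Make any power statement about variance from that second regression.

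If limits of agreement are reported and the spread changes with amount, give them by bottle size or on a log or percentage scale.

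The cost is one extra regression on data already collected and a few sentences of rewording. No participants or procedures are added.

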Each participant will, in random order, prepare 2 bottles of infant formula measuring 2 fluid ounces, 4 fluid ounces, 6 fluid ounces, and 8 fluid ounces. A total of 8 formula bottles will be prepared at Visit 1. Manufacturers' instructions state that 1 level scoop of powdered formula (8.8g) yields a 2 fluid ounce bottle, 2 unpacked level scoops of powdered formula (17.6g) yields a 4 fluid ounce bottle, 3 unpacked level scoops of powdered formula (26.4g) yields a 6 fluid ounce bottle, and 4 unpacked level scoops of powdered formula (35.2g) yields an 8 fluid ounce bottle. The Remote Food Photography Method and Directly Weighed Food Method will be utilized for each formula preparation as described below. Food weights (to the nearest tenth of a gram) will be measured using METTLER TOLEDO PB3001 scales. For each bottle, the participant will use the formula scoop provided to measure the required amount of powdered formula. The participant will dispense the correct number of scoops of powdered formula into the formula bottle depending on which size bottle is being prepared. After all powdered formula is dispensed into the clear formula bottle, the participant will capture a photo of the formula bottle with powdered formula only. This will be referred to as food provision. PBRC staff will weigh the formula bottle with powdered formula only. The participant will pour water into the bottle and mix the formula. Then, the participant will capture a photo of the prepared formula bottle. This will also be called food provision. PBRC staff will weigh the prepared formula bottle. Then, the PBRC staff will discard a random amount of the prepared formula. The participant will capture a photo of the formula bottle after the random amount of the prepared formula has been discarded. This will be referred to as waste. Then, PBRC staff will weigh the formula bottle. The captured photos will be used to determine if the RFBM accurately estimates simulated infant food intake.

which will be evaluated as food provision minus waste. This procedure will be repeated to assess intra-individual variability.

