### **6.3. Visit 2**

Participants will be asked to return to the IBL approximately 5 to 10 days later to complete Visit 2. At Visit 2, participants will be instructed to repeat the infant formula preparations from Visit 1. Participants will prepare 4 formula bottles at Visit 2. Each participant will, in a random order, prepare bottles that will provide 2 fluid ounces, 4 fluid ounces, 6 fluid ounces, and 8 fluid ounces of infant formula bottles.

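### Each participant gives 12 correlated photo–weight pairs, but the named tests have no participant term and the R² sample size counts one point per participant

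*Protocol*

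**What the plan says.** Section 6.2 has each participant make two bottles at each of 2, 4, 6 and 8 fl oz: "A total of 8 formula bottles will be prepared at Visit 1". Section 6.3 adds one more of each size: "Participants will prepare 4 formula bottles at Visit 2". Both methods are applied to every bottle: "The Remote Food Photography Method and Directly Weighed Food Method will be utilized for each formula preparation as described below". Each person therefore contributes 12 pairs, three per size.

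Section 9.1 counts participants. It states that an R² "of .14 can be detected with 53 participants (power = .80"), and that "the sample size was established based on the regression analysis used to do so since it required the largest number of participants". The same section calls the question answered by that regression critical to validity.

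Section 9.2 then names the tests: "Provision, waste, and intake will be compared using paired t-tests", plus Bland-Altman regression of error on amount, at alpha 0.05. It does not say whether the unit is the bottle, the participant, or the participant within a size. Repetition within a person appears only in the secondary aim, which concerns variability in preparation and not the validity analysis.

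**The concern.** An ordinary paired t-test and an ordinary regression both assume independent pairs. Twelve bottles scooped, poured and photographed by one person may share error. How the 12 pairs enter the analysis then matters in two ways.

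- If they are pooled, the standard error of the mean error is too small.
- If they are averaged, the spread in amount is lost. Everyone makes the same set of sizes, so the planned spread lies within participants, and the regression on 53 means has little left to work with.

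This affects the primary aim. The regression is the analysis that fixed the sample size, and the t-test decides whether the photographic method is said to be biased.

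**Working it through.** **Inputs from the protocol.** 12 bottles per person; 53 participants; 8.8, 17.6, 26.4 and 35.2 g of powder for the four sizes ("1 level scoop of powdered formula (8.8g) yields a 2 fluid ounce bottle" and multiples); "random discard of 10-90% of prepared bottle"; SD 9.71 g (Table 2) and 4.68 g (Table 3); two-sided alpha 0.05.

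**Assumptions not in the protocol.** Within-participant correlation of error (ICC) 0 to 0.30; between-person scoop CV 5–10%; about 30 g of prepared formula per fl oz; discard uniform over 10–90%; the table SDs taken as per-bottle SDs of error; a 10% proportional bias as the target; weighed amount as the regressor.

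**1. The plan's own figure.** Noncentral F with 1 and N − 2 df, λ = N·R²/(1 − R²). With R² = 0.14 and N = 53, λ = 53 × 0.14/0.86 = 8.63 and power is 0.82 (0.79 by Fisher z). The stated 53 is reproduced with one point per participant.

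The t-test tables do not rest on that basis. At n = 53, Table 3's 2.57 g matches two independent groups of 53; a paired test gives 1.84 g. Table 2's 4.95 g matches neither form (two-group 5.33 g, paired 3.81 g).

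**2. Pooled, paired t-test (53 × 12 = 636 pairs).** Design effect DE = 1 + 11·ICC; type I error = 2[1 − Φ(1.96/√DE)].

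| ICC | DE | Type I error |
|---|---|---|
| 0 | 1.00 | 5% |
| 0.05 | 1.55 | 12% |
| 0.10 | 2.10 | 18% |
| 0.30 | 4.30 | 34% |

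**3. Pooled regression.** Amount varies mainly within participants, so a shared intercept does not inflate the slope test. Simulated rejection of a true zero slope is about 1–5% when participants differ only in intercept. It is about 15–19% when they also differ in slope (slope variation set at 10% of error variance).

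**4. Averaged to 53 means, regression.**

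*Powder.* Across bottles the variance of amount is 96.8 g² (SD 9.8 g). Across participant means the SD is CV × 22 g = 1.1–2.2 g. The error variance of a mean is 4.68²(1 + 11·ICC)/12. With slope 0.1, R² is 0.0015–0.026 and power is 6–21%.

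*Intake.* Prepared weights of 60, 120, 180 and 240 g have mean square 27,000, and the discard fraction has variance 0.8²/12 = 0.0533. Bottle variance is 27,000 × (0.0533 + 0.25) − 75² = 2,565 (SD 51 g). The variance of a 12-bottle mean is 27,000 × 0.0533/12 = 120 (SD 11 g). R² is 0.132, 0.068 and 0.034 at ICC 0, 0.10 and 0.30; power is 80%, 49% and 27%.

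**5. Bottle level, powder.** R² = 0.968/(0.968 + 21.90) = 0.042. With 636 bottles and a common slope, power is over 99%. If participants' slopes vary (10% of error variance) and one slope per person is tested over 53 people, SE = √[(0.1 × 21.90/96.8 + 0.9 × 21.90/1,161.6)/53] = 0.0273, where 1,161.6 = 12 × 96.8. Then 0.1/0.0273 = 3.66 and power is about 95%.

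**6. By size, one bottle per participant, intake.** SD of amount is prepared weight × √0.0533.

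| Size | SD of amount | R² | Power |
|---|---|---|---|
| 2 fl oz | 14 g | 0.020 | about 18% |
| 4 fl oz | 28 g | 0.075 | 53% |
| 6 fl oz | 42 g | 0.155 | 86% |
| 8 fl oz | 55 g | 0.25 | 98% |

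For provision the nominal amount is constant within a size, so there is no planned range to regress on.

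**The case against.** The strongest reply is that the protocol neither pools nor averages. It leaves the unit open, and an analysis plan commonly settles how replicates enter. That is fair as far as it goes, and the consequences in steps 2 to 4 are conditional for that reason. But the protocol does fix the tests, the sample size and the analysis that drove it, and these do not fit a 12-bottle design as written.

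A reader might infer several stronger claims. The documents do not support them:

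- *No reading of the plan works.* The t-test on participant means is valid. Analysis by size with one value per participant is valid too, and it can test error over amount for intake at the larger sizes (step 6). Waste varies through the same discard, so it also keeps a range within a size.
- *Every pooled test is anti-conservative.* This is so for the t-test at any positive correlation. For the regression it requires participants to differ in proportional error.
- *Averaging makes the regression blind.* That is close to true for provision. For intake, the main outcome, the random discard keeps some spread, and power reaches 80% at zero correlation.
- *All of section 9.1 assumes one pair per participant.* Only the R² calculation reproduces that way.
- *The study is too small.* Analysed by bottle, it has ample information.

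It also stands that no document gives a correlation for the photographic error. If it is near zero, the pooled t-test is not inflated.

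**Conclusion.** The point holds as a gap between design and analysis: 12 clustered pairs per person, tests with no place for clustering, and a regression sample size that counts one point per person. The two simplest ways to fill the gap each damage one half of the primary analysis. Pooling puts the t-test at about 12–34% type I error for ICC 0.05–0.30. Averaging leaves the regression with 6–21% power for powder and 27–80% for intake at a 10% bias. Analysis by size avoids both for intake at the larger sizes, but the plan does not state it and it cannot do the job for provision.

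The direction of these effects follows from the design. Their size rests on the assumed correlation, scoop variation, prepared weight per fluid ounce and bias, and on SDs that section 9.1 borrows from beverages and condiments. This should be fixed before analysis. It does not threaten the data, which can support a sound analysis.

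**What to change.** Take the photographic estimate minus the weighed value for each bottle as the outcome, and use all bottles, including the 8 from Visit 1 for people who miss Visit 2. For each quantity (provision, waste, intake), fit a linear mixed model with weighed amount and visit as fixed effects, and a participant random intercept and random slope on amount. A simpler route with the same aim is one mean error and one slope per participant, each tested over participants.

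The random slope is needed. When participants differ in slope, an analysis with intercepts only rejected a true zero slope about 20–25% of the time in simulation, whereas per-participant slopes held about 4–6%.

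Report mean bias, slope and limits of agreement from this analysis, with the limits built from the between- and within-participant variance together. Restate the power paragraph on the same basis, including Tables 2 and 3, and state the assumed correlation.

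The cost is new analysis wording in section 9.2 and a revised power paragraph in section 9.1. No new data or participants are needed.
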